## Sample size and sampling method

The sample size is estimate based on similar studies on the lifestyle of infertile couples [24]. The comparison formula between two ratios will be used at the 95% confidence level The Cronbach’s α of 0.05 and power of 80% will be considered. Finally, 600 couples will be included in the study, of which 150 female and 150 males will be placed in the lifestyle program group and the rest in the control group.

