### Sampling, randomization, and blinding methods

After selecting the initial samples, the permuted block randomization will be done using a randomized block design with four blocks by a statistics consultant from a valid website (Sealed Envelope.Com or Randomization.Com). Then, the participants will be divided into two groups per the 1:1 allocation ratio. In this way, after listing all possible situations, 75 blocks of 4 will be created based on the sample size of 300 people. Then, by assigning a number to each of them, using a computerized random number table, with a ratio of 1:1, people will be divided into two intervention and control groups. Then, the subjects will be divided into two intervention and control groups. The numbers are placed in sealed envelopes in the order of each block generated. Each eligible patient who enters the room is then given an envelope. After that, they are assigned to one of these groups. Patient information will be recorded by the research team and confidentiality will be respected.

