## Data analysis

The data obtained from the first stage will be analyzed using a meta-analysis tool in RevMan. The data of the clinical trial will be assessed using descriptive and analytical statistics by SPSS software. According to the type of variables, chi-square tests for descriptive variables, determining the average statistical difference of two groups by t-test for independent groups will be used. Regression tests will be performed for the relationship between the variables and the normality of the data will be determined first Findings of the clinical trial will be included in a scientific article following academic standards or will become available in scientific meetings.

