## Discussion

Health-promoting lifestyle training program comprises a set of consistent activities, such as recommendations and training of skills regarding physical activity, diet, stress and anxiety adjustment methods, sleep hygiene, sleep disorders, adjusting meal portions, improving interpersonal relationships, considering self-actualization, paying attention to psychological health, learning methods of dealing with life problems, and avoiding general health risk factors. A couple is defined as a man and a woman in an emotional and sexual relationship, and there is an economic interaction between them. Couples’ lives and their interactions with each other affect their fertility health. One of the advantages of this study is the inclusion of infertile couples instead of individuals, which can improve the process of promoting health. In addition, they can reduce the pressure caused by infertility issues with collaboration. Another advantage of this study is its cost-effectiveness. Furthermore, couples could support each other and resolve problem together. The researcher will be in contact with the patients through face-to-face meeting in a private room in the infertility clinic or in other ways such as text messages, phone calls and social networking groups, providing daily relevant content and according to their needs and questions to is constantly in touch. This could be another benefit of this study. Furthermore, this study will be conducted by reviewing texts and methods examined up to the present and selecting the method with the highest score. One of the limitations of the study is the limited time for infertile people. Although scattered lifestyle training programs are considered separately for infertile women in Iran, the combined lifestyle training program is rarely used in infertility clinics. We hope that the results of this study will lead to the utilization and improvement of the health of infertile couples.

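### Both partners are enrolled and counted as persons, but the couple is never fixed as the unit of allocation and analysis, so the named tests can exceed their 5% error rate

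*Protocol article*

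**What the plan says.** The protocol article describes its sample in three ways.

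- Sample size and sampling method: "600 couples will be included in the study".
- The same sentence continues: "150 female and 150 males will be placed in the lifestyle program group and the rest in the control group".
- Sampling, randomization, and blinding methods: "75 blocks of 4 will be created based on the sample size of 300 people", at a 1:1 ratio, with one envelope handed to each eligible patient.

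The Data analysis section names the comparisons between arms: "chi-square tests for descriptive variables" and, for means, "determining the average statistical difference of two groups by t-test for independent groups will be used". It adds only that "Regression tests will be performed for the relationship between the variables", without giving a model.

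The abstract makes chemical and clinical pregnancy the initial outcome and live birth the secondary one. It also lists oocyte and embryo numbers, questionnaire measures, BMI and abdominal circumference. The Discussion presents the enrolment of couples as a strength and states: "Couples’ lives and their interactions with each other affect their fertility health".

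**The concern.** A couple has one pregnancy result between its two members. On questionnaire scores and body measures, the article's own remark that partners influence each other makes their values likely to be correlated. Chi-square and the two-sample t-test both require independent observations within and between arms. A sample counted in persons, combined with tests that have no couple term, invites two errors: entering each pregnancy twice, and pooling women and men as if they were unrelated. Either would make standard errors too small. For pregnancy this would affect the main outcome. Counting persons would also make the trial look better powered than it is.

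**Working it through.** **1. The plan's own figures.** The sample size cannot be reproduced, because the two-proportion formula is cited without a control rate, an effect or a dropout allowance. Only the counts can be compared.

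- 600 couples are 2 × 600 = 1,200 persons.
- 150 women + 150 men = 300 persons in the lifestyle arm. With 1:1 allocation this is 600 persons, or 300 couples, 150 per arm.
- 75 blocks × 4 = 300 allocations. This fits 300 couples with one allocation each. If the 300 are persons, as written, it means 150 couples in all.
- If 600 couples is taken literally, the remainder for control is 1,200 − 300 = 900 persons, which is not 1:1.

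The reading that best joins the second and third figures is 150 couples per arm with partners together. It is used below, but the article does not state it.

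**2. Pooled partners in the same arm.** For clusters of two with within-couple correlation ICC, the variance is multiplied by 1 + ICC. A test that ignores this has a true two-sided type I error of

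2 × (1 − Φ(1.96 / √(1 + ICC))).

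The article gives no ICC, so a range is assumed.

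| Assumed ICC | SE too small by factor | Effective n of 300 per arm | Type I error |
|---|---|---|---|
| 0.1 | 1.049 | 273 | 6.2% |
| 0.2 | 1.095 | 250 | 7.4% |
| 0.3 | 1.140 | 231 | 8.6% |
| 0.4 | 1.183 | 214 | 9.8% |
| 0.5 | 1.225 | 200 | 11.0% |

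A simulation (300 couples, 4,000 runs per setting) gave 7.0%, 9.1% and 9.9% at ICC 0.2, 0.3 and 0.5. This agrees apart from simulation error of about 0.4 to 0.5 points, with the last value about two such errors low.

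**3. Each pregnancy counted for both partners.** This is ICC = 1, and chi-square doubles: 2 × (1 − Φ(1.96 / √2)) = 16.6%. A simulation at an assumed pregnancy rate of 35% gave 16.4% on persons and 4.7% on couples.

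An illustration with assumed counts, without continuity correction:

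- Couples: 45/150 against 57/150, chi-square 2.14, p = 0.14.
- Same data as persons: 90/300 against 114/300, chi-square 4.28, p = 0.039.

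**4. Power.** At assumed rates of 30% and 41%, power is 51% with 150 couples per arm, but appears to be about 80% if 300 persons per arm are entered.

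**5. Other allocation patterns.**

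- Persons allocated individually: simulated type I error is 4.7% to 5.3%, because the within-couple covariance cancels on average.
- Partners always in opposite arms: the factor becomes 1 − ICC, and the error falls to 2.8% at ICC 0.2 and 0.6% at ICC 0.5.

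So the direction of the error depends on the allocation unit, which the article leaves unclear.

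**The case against.** A reader might infer that the plan treats partners as independent, that its questionnaire p-values are therefore too small, and that pregnancies will be double-counted. The article does not support this.

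- A t-test for independent groups is the ordinary name of the two-arm test. It describes the arms and says nothing about partners.
- No section says that women and men are pooled. Listing 150 of each sex fits separate analyses equally well.
- Pregnancy is observed in the woman, and nothing says it is entered for the man as well. Oocyte numbers and sperm parameters each belong to one partner.
- The wording of the randomisation section suggests allocation of individuals, under which the pooled t-test keeps roughly its nominal level.
- Questionnaire scores are named as neither the initial nor the secondary outcome, so inflation there does not touch the main result.
- A statistical analysis plan or full protocol may exist, and model details are commonly left to it.

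All of this stands against an unconditional claim, and the choice of mixed-model terms may indeed be left to an analysis plan. It does not remove the narrower point. The article itself commits to a head count and to named tests, and its counts contradict each other on the unit. Individual allocation is no way out either: a couple whose partners fall in different arms has no single arm to which its pregnancy belongs.

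**Conclusion.** The concern holds in conditional form. The article enrols couples, counts persons, names only tests that assume independent observations, and never fixes the couple as the unit.

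- If partners share an arm, the sexes are pooled and the within-couple correlation is positive, type I error for questionnaire and body measures is about 6% to 11% (ICC 0.1 to 0.5).
- If pregnancies were counted per person with partners in the same arm, it would be 16.6%.
- If pregnancy is analysed once per couple and the sexes separately, with the couple as the unit of allocation, the named tests are valid.

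The ICC values, pregnancy rates and example counts are assumptions. The 16.6% follows from duplication alone and needs no assumed ICC. That partners share an arm is the natural reading of the sample-size section but is not stated. This should be settled before any comparison of arms, because it determines the denominator of the main outcome.

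**What to change.** 1. State that the couple is the unit of allocation, with one envelope per couple and both partners in the same arm. If allocation has already been done differently, report how it was done and adapt the analysis to it.
2. Reconcile the 600 couples, the 150 women and 150 men, and the 300 people across the sample-size and randomisation sections, and give the number of couples per arm.
3. Analyse pregnancy, live birth, and oocyte and embryo numbers with one record per couple.
4. Analyse questionnaire scores, BMI and abdominal circumference separately for women and men, or in a linear mixed model with a random intercept for couple and fixed effects for arm and sex.

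The cost is wording. The software already named can fit the mixed model. Compared with a pooled test that ignores couples, confidence intervals for the arm difference widen by about 5% to 22% (√1.1 = 1.049 to √1.5 = 1.225 over the assumed ICC range), which is their correct width. Analysis by sex gives two comparisons per measure instead of one.

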## Discussion

Health-promoting lifestyle training program comprises a set of consistent activities, such as recommendations and training of skills regarding physical activity, diet, stress and anxiety adjustment methods, sleep hygiene, sleep disorders, adjusting meal portions, improving interpersonal relationships, considering self-actualization, paying attention to psychological health, learning methods of dealing with life problems, and avoiding general health risk factors. A couple is defined as a man and a woman in an emotional and sexual relationship, and there is an economic interaction between them. Couples’ lives and their interactions with each other affect their fertility health. One of the advantages of this study is the inclusion of infertile couples instead of individuals, which can improve the process of promoting health. In addition, they can reduce the pressure caused by infertility issues with collaboration. Another advantage of this study is its cost-effectiveness. Furthermore, couples could support each other and resolve problem together. The researcher will be in contact with the patients through face-to-face meeting in a private room in the infertility clinic or in other ways such as text messages, phone calls and social networking groups, providing daily relevant content and according to their needs and questions to is constantly in touch. This could be another benefit of this study. Furthermore, this study will be conducted by reviewing texts and methods examined up to the present and selecting the method with the highest score. One of the limitations of the study is the limited time for infertile people. Although scattered lifestyle training programs are considered separately for infertile women in Iran, the combined lifestyle training program is rarely used in infertility clinics. We hope that the results of this study will lead to the utilization and improvement of the health of infertile couples.

## Data Availability

Study data will be made available at completion of the study.

## Abbreviations

ART: Assisted reproductive technique
IVF: In vitro fertilization
ICSI: Intra cytoplasmic sperm injection
HPLII: Health promoting lifestyle II
BDI: Beck depression inventory
FFQ: Food frequency questionnaire
IPAQ: International physical activity questionnaire
NCD_S_: Non communicable diseases
FBDG: Food based dietary guideline
SPSS: Statistical Package for the Social Sciences
DASH: Dietary approach to stop hypertension
ESHRE: European Society of Human Reproduction and Embryology
SPIRIT: Standard Protocol Items: Recommendations for Interventional Trials
